## Methods/design

### Design

This study is an unblinded, non-randomized, multi-centre (4 sites), double-arm, controlled trial with 1:1 assignment. The duration of the study is 3 years and includes literature review, development of the app, clinic and patient recruitment, intervention delivery, as well as, data collection and analysis.

### Participants and recruitment

Patients scheduled for THR or TKR will be consecutively recruited in 4 German hospitals in urban and rural areas conducting between 364 and 2300 joint replacement surgeries per year. In addition, the hospitals are publicly, privately and financially associated by the employers’ liability insurance association. The recruitment of the participating patients will be done on initial contact by the inpatient physician and a project coordinator from January 2019 until October 2019 (Fig. 1).

**Fig. 1 Fig1:**
[figure not shown]
Flow chart of participants in the pabee study

A random assignment of the participants and simultaneous treatment of intervention and control group would carry the risk that people in the control group might learn about the app and its contents from patients of the intervention group. In order to prevent diffusion of treatment effects among participants, patients scheduled for preoperative consultation from January 2019 to May 2019 will be assigned to the control group and patients scheduled for preoperative consultation from June 2019 to October 2019 will be assigned to the intervention group.

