### Control group

The control group will receive standard care as provided by their hospital. This consists of verbal information about the perioperative treatment. Some clinics provide specific folders about the surgery process.

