### Data analysis

Baseline data, clinical and demographic characteristics will be presented to show the baseline comparability of the intervention group and the control group. The analysis will include all patients following the intention-to-treat principle, drop-out and loss to follow-up will be described. Data will be checked for completeness and normality. The treatment effect will be evaluated by the change in ADL using between group analyses, such as independent t-test and ANCOVA to adjust for demographic factors such as age, sex, BMI (body mass index), baseline pain, anxiety, joint, comorbidities, physical activity, pain medication, type and duration of rehabilitation and social support on change in outcomes. For comparison within groups paired t-tests will be conducted. Within the intervention group the relationship between usage metrics and patient reported outcomes will be analysed using linear regression analyses.

All statistical analyses will be performed using IBM SPSS Statistics for Windows, version 24 (IBM Corp., Armonk, N.Y., USA).

Results of the study will be presented at conferences and placed in journals.

The controlled trial will be accompanied by multi-perspective qualitative research approaches to understand user decisions and long-term user engagement of the intervention. These studies will be reported elsewhere.

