## Discussion

The aim of the study is to enhance patient reported outcomes after surgical hip or knee replacement by using mHealth with evidence-based content and interface.

It seems reasonable to bring patient education to the next level and adapt it to the needs and conditions of modern society. In recent years, the concepts of eHealth (Electronic Health) and mHealth have become increasingly important in patient-centred health care aiming to enhance patient involvement and self-management capabilities [19, 20]. mHealth intends to capitalize on people’s ubiquitous access to mobile phones to provide 24/7 health care [51]. Ideally, it leads to improved health outcomes by increasing patient knowledge, providing social support, enhancing patient-provider communication and saving resources at the same time [52].

However, there is a lack of evidence for the effectiveness of the use of mHealth in patients undergoing joint replacement [53, 54]. This study will investigate the effects of an evidence-based mobile app as an educational intervention on patient reported outcomes of this target group.

Numbers of joint replacements are increasing and shorter hospital stays require solid self-management skills. Evidence supporting the use of mHealth to potentially improve patient outcomes is of particular importance to open up new possibilities for patient care.

A major limitation of the study is the non-randomized assignment of participants. Therefore the comparability of the groups regarding all relevant patient characteristics will be comprehensively analysed.

A second limitation is a potential mode effect due to different survey modes (online based vs. tablet based) at baseline and 3 months post-surgery.

Another limitation and potential source of bias is the exclusion of participants assigned to the intervention group, but who failed to download or access the app. We have chosen to do this because those participants miss out on engaging with app contents for the preoperative phase that are expected to have an effect on primary and secondary outcomes. We will, however, analyse and report patients’ reasons for not engaging and consider this aspect regarding the generalisability of our findings.

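### Add hospital to the primary ANCOVA, because consecutive cohorts leave site mix free to shift between arms, and name calendar time as a limitation that no covariate can repair

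*Protocol article*

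**What the plan says.** The Design section describes an "unblinded, non-randomized, multi-centre (4 sites), double-arm, controlled trial with 1:1 assignment". Allocation is by consultation date (text after Fig. 1): "patients scheduled for preoperative consultation from January 2019 to May 2019 will be assigned to the control group". Those seen between June and October of that year form the app arm. The same dates apply to every site, and the stated reason is to stop knowledge of the app spreading to controls.

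Participants and recruitment describes consecutive enrolment in "4 German hospitals in urban and rural areas conducting between 364 and 2300 joint replacement surgeries per year", with different types of ownership. Under Control group, standard care is not uniform: "Some clinics provide specific folders about the surgery process". The Exclusion criteria remove patients who have not downloaded the app by admission, in the intervention group only.

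Data analysis states: "The treatment effect will be evaluated by the change in ADL using between group analyses, such as independent t-test and ANCOVA". The factors named are age, sex, BMI, baseline pain, anxiety, and then "joint, comorbidities, physical activity, pain medication, type and duration of rehabilitation and social support on change in outcomes". Counting rehabilitation once, that makes eleven, and neither hospital nor calendar time is among them. Structural hospital data are collected to compare and describe the sites (end of the Outcomes section), with no stated role in the model. The Discussion calls non-randomized assignment a major limitation and answers it this way: "the comparability of the groups regarding all relevant patient characteristics will be comprehensively analysed".

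**The concern.** In a before-and-after comparison across several hospitals, two things other than the app can differ between arms without any patient characteristic showing it.

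- **Site mix.** If a hospital whose patients improve more, or less, contributes a larger share in one period, its effect is credited to the app or held against it. Omitting hospital also leaves between-site variance in the error term.
- **Calendar time.** All controls are enrolled before all app patients, at every site. Any seasonal or secular change in self-reported daily function therefore enters the app estimate in full.

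The remedy in the Discussion looks at patient characteristics, which reaches neither mechanism directly.

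**Working it through.** **Inputs from the protocol.** Target difference 10 points, SD 15, 58 evaluable patients per joint (29 per arm), 116 in all (58 per arm), 160 recruited; 364 to 2300 operations a year (2300/364 = 6.3-fold); consultation windows as quoted; baseline 4–6 weeks before surgery; outcome at 3 months.

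**The plan's own figures.** A one-sided t-test at 0.05 needs 29 per arm (power 0.806), which gives 58 per joint. Two-sided would need 37 per arm, or 74. The protocol does not state sidedness, and the point here does not turn on it. Inflation: 116/(0.80 × 0.95 × 0.96) = 159.0, in line with 160.

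**Site mix.** Bias = gap between sites in ADL change × shift in enrolment share. The documents give neither quantity, so both are assumed:

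| Gap (points) | Shift 10 pp | Shift 20 pp | Shift 30 pp |
|---|---|---|---|
| 5 | 0.5 | 1.0 | 1.5 |
| 10 | 1.0 | 2.0 | 3.0 |

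The standard error of the unadjusted difference at 58 per arm is 15 × √(2/58) = 2.8 points.

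**Cost of a hospital term.** With equal site shares in both periods, the arm effect keeps 100% of its information. The 3 degrees of freedom move the two-sided critical t from 1.9810 (114 df) to 1.9816 (111 df). With equal arms and unequal shares p (control) and q (app), the fraction retained is 2 × Σ pq/(p+q). For shares of 25/25/25/25% against 45/25/15/15%, this is 2 × (0.1607 + 0.1250 + 0.0938 + 0.0938) = 0.95.

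**Calendar overlap.** Take surgery 4 to 6 weeks after consultation and the outcome 91 days after surgery.
- Control: 1 January + 28 + 91 days = 30 April 2019; 31 May + 42 + 91 days = 11 October 2019.
- App: 1 June + 28 + 91 days = 28 September 2019; 31 October + 42 + 91 days = 12 March 2020.

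The overlap is 28 September to 11 October, two weeks. Data collection procedures allows some consultations more than 6 weeks before surgery, which moves some outcome dates later in either arm. Enrolment dates do not overlap at all.

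**What a calendar shift would do.** With no true effect and a shift of b points (assumed), the two-sided rejection rate comes from a noncentral t with noncentrality b/(15√(2/n)):

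| b | 58 per arm | 29 per arm |
|---|---|---|
| 2 | 11% | 8% |
| 3 | 19% | 12% |
| 5 | 43% | 24% |

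**Whether modelling time helps.** Assume equal enrolment per site and month and a hospital term in the model. Under the common switch, calendar-month effects leave 0% of the information on the arm effect, and a linear trend leaves 24% (about 28 of 116 patients). If two hospitals switched two months later and recruited two months longer, hospital plus month effects would leave about 15% (about 17 of 116). The standard error would then be 15 × √(4/16.9) = 7.3 points, and two-sided power for 10 points about 27%.

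**The case against.** The strongest reply has four parts.

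1. **The covariate list is open.** It is introduced as a set of examples, and an analysis plan not shown could contain a hospital term. This stands in part: the protocol does not rule hospital out. But it spells out eleven factors and leaves out the unit within which both cohorts are recruited, so naming hospital is a concrete improvement.

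2. **Site is not confounded with the app by design.** This stands. A reader might infer from the six-fold volume range and the differing standard care that site and app cannot be told apart. Those are contrasts between hospitals. Nothing restricts a hospital to one period, and bias arises only if shares shift. No shift is documented. The one stated rule that could plausibly produce one is the download exclusion, which acts in the app arm alone and could act unevenly across hospitals.

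3. **The site bias is assumed and modest.** This also stands. The outcome is change in ADL, so stable site differences in level largely cancel, and the assumed gap must be a gap in improvement. At most combinations in the table the bias is well under one standard error.

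4. **The sequential design is deliberate, and non-randomization is declared.** The contamination argument is reasonable, and structural hospital data are collected. Yet the declared limitation names neither season nor secular change, and its remedy covers only patient characteristics.

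A reader might also infer that the trial needs fixed enrolment cells or staggered switch dates. Closing cells at a quota conflicts with consecutive recruitment, and per-site targets are operational detail that an article may omit. A two-month stagger makes the effect estimable with month effects, but too imprecisely to serve as the primary analysis.

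**Conclusion.** The point holds in two parts of different kind.

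**Site** is a modelling gap that costs almost nothing to close. The possible bias is 0.5 to 3.0 points against a 10-point target, resting wholly on assumed site differences in change of 5 to 10 points and assumed share shifts of 10 to 30 percentage points. The documents do not show that such a shift will occur, only that no stated rule prevents it.

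**Calendar period** is fully aliased with arm at enrolment and almost fully at the outcome date, given 4 to 6 weeks to surgery. No covariate, hospital included, repairs this while all sites switch together. The size and direction of any seasonal or secular effect are unknown. The aliasing is established; a bias of a given size is not.

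**What to change.** 1. Name hospital as a fixed effect in the primary ANCOVA, overall and in the separate knee and hip analyses. Cost: a line of analysis wording, 3 degrees of freedom per model, and almost no information unless site shares shift, in which case the small loss is the price of removing the bias.
2. Report enrolment, and exclusions for not downloading the app, by hospital, joint and period, so that any shift in site mix is visible. Cost: one table from data already collected.
3. In the limitations, state beside non-randomization that arm coincides with calendar period at all four hospitals, so that seasonal and secular change cannot be separated from the app. Word the conclusion as a difference between consecutive cohorts, adjusted for hospital and patient factors, and not as an effect of the app alone. Cost: text, and a more restrained claim.

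Fixed cell quotas and a staggered switch are not recommended as primary remedies, for the reasons given above.

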### Eligible patients must meet the following inclusion criteria

scheduled for primary unilateral THR or TKR18 years of age or olderable to speak and understand GermanSigned informed consent (on paper)have a smart phone

### Exclusion criteria

emergency hip or knee replacement surgery, such as after a fallrevisions or exchange surgeryPatients already received a replacement of another joint in the pastcognitive impairments of all types (as assessed by the attending physician)mental illnesses of all types (as assessed by the attending physician)Patients, who have not downloaded the app when they were admitted to the hospital (intervention group)post-surgical complications, such as infections, allergies, instability, delirium, or otherlimited language skills preventing proper app use or completion of questionnaires

Participants assigned to the intervention group who failed to download or access the app will be excluded. However, project coordinators of the participating hospitals will interview those participants and record their reasons for not engaging with RECOVER-E. These data will be analysed and reported as part of the sample description.

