#### Information and education

Comprehensive text and video material aim to educate the patients and provide information on the disease, the artificial joint, the joint replacement procedure and everyday life after surgery. The preoperative phase focuses on information on the physiology of knee or hip, osteoarthritis, as well as, pain and pain management, but also gives a preview of daily activities with an artificial joint and support possibilities.

Patients will be prepared for the hospital stay and surgery by giving information on how to deal with allergies, general preparation for surgery, medication especially on pain and other pain management interventions [27].

The intra- and postoperative phase contains information on the hospital stay and the procedure itself, complications and how to prevent them, wound care, bowel function and body hygiene.

In the rehabilitative phase and home environment, users are encouraged to take part in their pain management, as well as, in their wound and scar care by frequent monitoring with the tools provided in the app. They are given information on rehabilitation, sports, sleep, sexual activity and returning to work post surgery. Users are offered 8 video clips with short and simple exercises to train muscles and increase flexibility in the legs for either knee or hip surgery (e.g. seated leg extension, elevation of legs while sitting) [31].

RECOVER-E proposes a certain number of repetitions and sets per exercise, which gradually increase after hospital discharge and after rehabilitation to keep training motivationally attractive. However, users are requested to first consult their physiotherapist to individually decide on the appropriate exercise intensity at any stage.

Since emotional well-being is closely and positively linked to the experience of control over one’s own recovery process, RECOVER-E provides important information on symptoms and self-management in the immediate postoperative phase. The app also motivates users to ask family and friends for support in order to bridge difficult and frustrating time periods during the first weeks after surgery [32].

Overall RECOVER-E’s education abilities aim to prepare users for an everyday, joint-sensitive life after their joint replacement surgery.

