#### Communication

The app comprises an interface for the clinical care teams. This will be used by participating hospitals to provide customized information on centre-specific procedures, teams and other information, the hospitals want to share regarding the organisation of the surgery and hospital stay. Additionally, health data provided by users in their app-based monitoring can be transferred to a specific web site accessible only by clinicians of the participating wards. Users have to give individual permission to transfer information from the pre-hospital and hospital phase only. That information can support the problem-centred conversations with nurses and doctors and give insight on pain- and function-based problems during the preparation phase of the surgery and after the operation.

Another feature to facilitate communication after discharge is an automatic message service to inform the users’ orthopaedist in case of complications after discharge: back at home users are instructed to continue self-assessment of pain, function and to observe their wound. If thresholds are exceeded, the app offers to inform the orthopaedist via fax. Users are free to decide on each individual occasion whether or not that information should be sent to their orthopaedist. They are told to visit a doctor immediately in case they observe a further decline in their health.

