### Outcomes

Data presented in Table 1 will be measured in the study.

**Table 1 Tab1:** Study measures to be collected

Measure	Instrument	t_0_	t_1_	t_2_	t_3_	t_4_
Primary outcome measure						
Activities of daily living (ADL)	KOOS/HOOS subscale ADL (self-reported)	x				x
Secondary outcome measures						
Pain, symptoms, Sport & Rec and quality of life	KOOS/HOOS subscales pain, symptoms, Sport & Rec and quality of life (self-reported)	x				x
Pain at rest	NRS (self-reported)	x	x	x	x	x
Pain during activity	NRS (self-reported)	x	x	x	x	x
Preoperative anxiety and depression	HADS (self-reported)	x	x			
Other measures						
Usage metrics	number of user sessions, length of time participants interact with the app, content they engage with, frequency of recording self-monitoring parameters, number of awards	continuous recording				
Physical activity	IPAQ (self-reported)	x				
Social support	questionnaire (self-reported)					x
Physician visits post-surgery	questionnaire (self-reported)					x
Use of pain medication	medical record, questionnaire (self-reported)		x	x	x	x
Sex, age	medical record				x	
BMI (size, weight)	medical record				x	
Operated joint	medical record				x	
OPS, ICD	medical record				x	
Comorbidities	medical record				x	
Duration of hospital stay	medical record				x	
Type and duration of planned and performed rehabilitation programme	medical record, questionnaire (self-reported)				x	x
Complications post-surgery	medical record, questionnaire (self-reported)			x	x	x
Structural data of hospitals						
- Number of beds - Number of joint replacement surgeries performed over the past 12 months - Number of nurses in the orthopaedic departments: nurses, nursing assistants, Pain Nurses, full-time equivalent - Number of physicians in the orthopaedic departments: total number, number of orthopaedic specialists, full-time equivalent - Process quality management data for the care of patients with THR/TKR (documentation forms and guidelines, interprofessional standard operating procedures for analgesic therapy, pain management guidelines, other pain therapy guidelines, standard operating procedures for patients with THR/TKR, special contracts with other facilities and mandatory health insurance companies for structured patient care) - Regular cooperation with institutions of inpatient or outpatient rehabilitation						

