### Sample size

Based on the primary outcome ADL subscale of the KOOS/HOOS and the assumable clinical relevant change of 10 points [37, 44, 45], we expect that the group using the mobile app in addition to the standard care will improve at least 10 points more than the control group after having undergone TKR/THR 3 months post-surgery.

To allow for separate analysis of patients with knee and hip OA, 58 knee patients and 58 hip patients are required to detect a difference of 10 points on the HOOS/KOOS ADL subscale (SD 15, power = 0.80 and α = 0.05) [37, 44, 46]. Allowing for 20% dropout [47–49], 5% complications post-surgery [50] and 4% erroneous records, a total of 160 patients will be recruited.

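### Excluding patients with post-surgical complications contradicts the intention-to-treat statement and selects, after assignment, on something the app may influence

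*Protocol article*

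**What the plan says.** - **Exclusion criteria** (Protocol article): the list includes "post-surgical complications, such as infections, allergies, instability, delirium" and then an open category. No severity threshold or time window is given. Unlike the criterion on downloading the app, it is not limited to the intervention group.
- **Sample size:** the inflation allows for "5% complications post-surgery", beside 20% dropout and 4% erroneous records, to reach 160.
- **Data analysis:** "The analysis will include all patients following the intention-to-treat principle".
- **Participants and recruitment; Intervention group:** the cohort is set by the date of the preoperative consultation (January to May control, June to October app). App access follows directly after baseline, 4–6 weeks before surgery.
- **App content:** the hospital-phase material covers "complications and how to prevent them, wound care, bowel function and body hygiene". After discharge a message service can reach the user's "orthopaedist in case of complications after discharge". "If thresholds are exceeded, the app offers to inform the orthopaedist via fax", and the user decides each time whether to send. The Reminder section adds prompts for pain and wound observation.
- **Table 1:** a row "Complications post-surgery" is scheduled at t2, t3 and t4, from the medical record and self-report.
- **Discussion:** the exclusion of patients who did not download or access the app is named as a source of bias. The exclusion for complications is not mentioned.

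**The concern.** A complication of surgery cannot be known when a patient enters either cohort. Used as an exclusion, it removes people after assignment and, in the app cohort, after weeks of possible exposure. Those removed are likely to include some of the poorest recoveries.

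This matters for two reasons. First, an analysis that drops these patients is not an intention-to-treat analysis of all patients, so the two statements cannot both describe the primary analysis. Second, only the app cohort receives the extra information, self-monitoring and alerts, so complications might occur less often there or be noted more often. The catch-all category leaves room for judgement, staff know which cohort they are dealing with, and the cohorts run in different calendar periods. If removal differs by arm, the remaining groups differ in a way that an ANCOVA on baseline factors does not correct.

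**Working it through.** **Step 1. Does the exclusion act on the analysis set?** The inputs come from the Sample size section: 58 knee + 58 hip = 116 evaluable patients (taken as given here), losses of 20%, 5% and 4%, and 160 recruited.

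- All three losses applied in sequence: 116 / (0.80 × 0.95 × 0.96) = 116 / 0.7296 = 158.99, i.e. 159. This agrees with 160.
- Losses added: 116 / (1 − 0.29) = 163.4, i.e. 164. This is also near.
- Without the complication loss: 116 / (0.80 × 0.96) = 116 / 0.768 = 151.04, i.e. 152 (added form: 116 / 0.76 = 152.6, i.e. 153).

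The plan therefore counts patients with complications as lost to the analysis. At its own rate that is 0.05 × 160 = 8 patients.

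**Step 2. The statements side by side.** The exclusion criteria and the sample size remove these patients. The data analysis section includes everyone. The article gives no rule that reconciles the two.

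**Step 3. How large could the distortion be?** The article gives no complication rate by arm and no ADL deficit after a complication, so everything here except the 5% is assumed. Let p_c and p_a be the complication proportions in the control and app arms, and D the ADL shortfall of complicated cases. The part of the all-patient difference carried through complications, which exclusion removes, is (p_c − p_a) × D:

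| p_c | p_a | D = 10 | D = 20 | D = 30 |
|---|---|---|---|---|
| 5% | 2.5% | +0.25 | +0.50 | +0.75 |
| 5% | 7.5% | −0.25 | −0.50 | −0.75 |
| 10% | 5% | +0.50 | +1.00 | +1.50 |
| 20% | 10% | +1.00 | +2.00 | +3.00 |

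A positive entry is app benefit that the exclusion hides. A negative entry is app harm that it hides.

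Two variants at 5% give similar sizes:

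- **More recording only.** Suppose 7.5% are excluded in the app arm, while the matching extra 2.5% stay unrecorded among controls. The retained control mean then falls by (0.025 / 0.95) × D = 0.26 to 0.79 points for D = 10 to 30, which flatters the app. This gives unrecorded cases the full deficit, although they are probably milder.
- **Prevention in frail patients.** Suppose the app halves the rate, and those spared still score F = 10 to 20 points lower. The retained app mean then falls by (0.025 / 0.975) × F = 0.26 to 0.51 points, which counts against the app.

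**Step 4. What keeping these patients does to numbers.** Expected evaluable patients from 160 recruits rise from 160 × 0.7296 = 116.7 to 160 × 0.768 = 122.9.

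**The case against.** The rule is prespecified, worded for both arms and budgeted in the sample size. Function after an uncomplicated recovery is a legitimate, narrower question. The app's stated aims are training needs, adherence, self-care and motivation, and no hypothesis concerns complications. Prevention is one information topic among several. The alert is optional and goes to the patient's own orthopaedist, and nothing says that it feeds the trial's complication record. A difference between arms is therefore possible but not documented.

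Much of this stands. A complication-free analysis would be acceptable if labelled as such; the fault is that the article calls its analysis intention-to-treat. The objection on size also stands, since at 5% the effect is a fraction of a point.

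A reader might infer more than the documents support:

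- **That the trial cannot compare complications, or that recording them is pointless.** Table 1 collects them three times with no limit to one arm, and that record may be how the exclusion is applied. What is in doubt is the t4 outcome of excluded patients.
- **That the rule favours the app.** More recording would favour it, while prevention would count against it. The article does not settle which applies.
- **That a bias of 1 to 2 points is to be expected.** With D = 20, (0.10 − 0.05) × 20 = 1.0 and (0.15 − 0.05) × 20 = 2.0. These need recorded complications to double or triple in the app arm, for which the article gives no basis.
- **That complications generally come months after assignment.** App access is 4–6 weeks before surgery, and recording starts on the first postoperative day.

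**Conclusion.** The point holds as a contradiction about the primary analysis set, joined to a selection after assignment on a variable that the intervention may affect. It should be fixed, but it is not shown to threaten the trial's main conclusion.

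The contradiction rests on the text alone. The size rests on assumption: a control rate of 5%, halved or raised by half in the app arm, and a deficit of 10–30 points give about 0.25–0.75 points in either direction, against a target difference of 10. It becomes larger only if rates are higher or differ more between arms, up to 3 points at a 20% control rate in the range examined. The issue is who is analysed, not power. The article's limitations should have named this exclusion beside the one for not downloading the app.

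**What to change.** - Delete post-surgical complications from the exclusion criteria and keep these patients in the primary analysis by assigned cohort.
- Seek the t4 questionnaire from them in both arms under the same rule.
- Report the complications already scheduled for collection, by arm.
- Show the complication-free subset only as a labelled sensitivity analysis.
- Remove the 5% allowance from the sample size. The 160 can stay.

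**Cost:** a change of wording and t4 follow-up for about 8 patients. ADL variance may rise slightly. The Trial status section has control recruitment under way in May 2019 and the app still in testing, so the app cohort can follow the new rule from the start. Controls already excluded should be brought back and asked for t4. Their data may be late or incomplete, which would itself create a difference between arms, so completeness of t4 among patients with complications should be reported by arm.
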